### Description of PROMs

#### Disease-specific PROMs

*ESAS-r: Renal:* The Edmonton Symptom Assessment System, or ESAS, is a clinically validated and reliable symptom measurement tool, extensively used for a number of chronic diseases including cancer, heart disease, and kidney disease (Table 2). The original tool was developed by the Regional Palliative Care Program, Capital Health in Edmonton, Alberta [49]. The ESAS-r: Renal was modified from the original ESAS and validated for use with CKD patients in Canada to assess symptom burden [44]. Despite its widespread use in dialysis units in Canada, the use of ESAS-r: Renal has largely been limited to measurement of symptoms without systematic reporting of results to clinicians.

**Table 2 Tab2:** Comparison of PROMs in the EMPATHY Trial

	ESAS-r: Renal	IPOS-Renal	EQ-5D-5 L
**Type of PROM**	Disease-specific (renal) measure	Disease-specific (renal) measure	Generic, preference-based HRQL measure
**Use by Renal Programs**	•AKC-N •ORN •Study groups 1 and 3	•AKC-S •Study groups 1 and 3	•AKC-N •AKC-S •ORN •Study groups 2 and 3
**Measurement Properties**	•Clinically validated and reliable •Sensitive to change	•Clinically validated and reliable •Sensitive to change	Limited evidence for clinical use •Produces utility scores •Comparison with any population, including population norms
**Content**	Symptoms: •Pain •Tiredness •Drowsiness •Nausea •Lack of appetite •Shortness of breath •Depression •Anxiety •Wellbeing •Itch •Problems sleeping •Restless legs	Symptoms: •Pain •Shortness of breath •Weakness or lack of energy •Nausea •Vomiting •Poor appetite •Constipation •Sore or dry mouth •Drowsiness •Poor mobility •Itch •Difficulty sleeping •Restless legs •Changes in skin •Diarrhea •Anxiety •Depression Other: Information needs, practical concerns, family anxieties, and overall feeling of being at peace	Problems: •Mobility •Selfcare •Usual activities •Pain/discomfort •Anxiety/depression Visual Analogue Scale: overall health state
**Number of items/dimensions**	12	26	5 + VAS
**Scale**	0–10	0–4	5 dimensions: 1–5 categorical Index score: 0-dead, 1-full health VAS: 0–100

#### IPOS-renal

The Palliative care Outcome Scale, or POS, was developed in 1999 [50] for use with patients with advanced disease, and to improve outcome measurement by evaluating important outcomes in palliative care (Table 2). The Integrated Palliative care Outcome Scale, or IPOS, integrates questions from three different POS measures, incorporating symptoms, information needs, practical concerns, family anxieties, and overall feeling of being at peace. The IPOS-Renal contains all the elements of the IPOS, and the most common symptoms renal patients experience. The IPOS-Renal has also demonstrated validity and reliability and has been studied in dialysis and non-dialysis CKD patients in Australia [45].

### Generic PROM: EQ-5D-5L

The EQ-5D-5L is a generic preference-based measure of HRQL and has been selected as the PROM of choice in many clinical areas and settings (Table 2). The EQ-5D-5L includes a health status classification system with five dimensions (mobility, self-care, usual activities, pain/discomfort, anxiety/depression), each with five levels of problems (1 = none, 2 = mild, 3 = moderate, 4 = severe, 5 = extreme), describing 3125 distinct health states [46] [51]. An index score for each health state can be calculated using population preferences [52], which can then be used to estimate quality-adjusted life years (QALYs) in economic evaluations of health interventions or innovations [53]. Empirical evidence on the clinical application of the EQ-5D-5L with regards to individual patient care is limited, but a recent review of PROMs in CKD recommended the EQ-5D-5L for use in this patient population [54].

### Treatment aids

Treatment aids are assessment and treatment resources developed by expert clinicians for the management of certain symptoms and disorders. Each renal program developed treatment aids specific to symptoms assessed by the ESAS-r: Renal or IPOS-Renal (e.g., itchiness, restless leg syndrome, nausea) and the EQ-5D-5L (e.g., pain, anxiety/depression). Treatment aids are intended to support clinicians in the assessment and management of symptoms identified by these PROMs and will be made available for all clinicians at all study sites regardless of the group to which they are randomized.

Patient-facing materials are also provided to patients, to help them better understand the reasons why their symptom/problem may have developed, treatment options that might be considered, as well as self-care activities they can undertake to alleviate the symptom or problem.

### Clinician training

Nurses were responsible for administering PROMs to patients. They received training on the use of the ESAS-r: Renal or IPOS-Renal and/or EQ-5D-5L, depending on their study group allocation, which included an overview of the instruments, interpretation of patients’ scores from one measurement and changes in scores over time, the use of PROMs data during clinical visits (i.e. referring to treatment aids or clinical guidelines), as well as data entry in the EMR, if applicable. A toolkit for using PROMs in the dialysis unit was developed and shared with all clinicians in all participating dialysis units. A train-the-trainer model was adopted, where clinical nurse educators will receive training and subsequently provide on-site training to other nurses. Training was administered in a series of webinars and workshops. Figure 3 demonstrates the workflow whereby nurses were trained. Nephrologists received training through in-person presentations and print materials.

**Fig. 3 Fig3:**
[figure not shown]
Nurse Workflow of EMPATHY Intervention

### Primary and secondary outcome measures

The *primary outcome* in this study is patient-provider communication, which is assessed using a modified version of the Communication Assessment Tool (CAT) [55].

*Secondary outcomes* include:
HRQL, assessed using the EQ-5D-5L. [46].Symptom burden, assessed using the ESAS-r: Renal [44] or IPOS-Renal [45] and symptom management through the EMR.Anxiety and depressive symptoms, assessed using the Generalized Anxiety Disorder 2-items questionnaire (GAD-2) [56] and the Patient Health Questionnaire 2-items (PHQ-2) [57], respectively.Patient experience with their disease management, assessed using the Patient Assessment of Chronic Illness Care 11-items questionnaire (PACIC-11) [58].Healthcare utilization (e.g., physician, emergency department and hospitalization), assessed through linkage with provincial administrative health care databases at the individual patient-level.

Demographic characteristics and the outcome measures are collected at baseline, 6-months, and 12-months. Data on medical history, dialysis history, and clinical measures are collected from patient charts.

### Sample size and power

The EMPATHY trial is a pragmatic clinical trial with a sample size determined based on eligibility of hemodialysis units and its encompassing patients. Our intention was to enroll all eligible dialysis units within the province of Alberta, and a sample of eligible units in Ontario. Therefore, we did not calculate an optimal sample size for adequate power to detect statistical significance. From 44 dialysis units, we will be utilizing data from approximately 3000 patients. Based on an estimated intraclass correlation of 0.1 and a standard deviation for the CAT (primary outcome measure) of 0.74 (based on pilot data from HD patients in Alberta), this will provide 80% power to detect an effect size of 0.23 with a two-tailed test at typical level of significance, α = 0.05 [59]. While this is a small effect size for the primary outcome, we are nonetheless confident in the design, given that this is a pragmatic quality improvement study, involving 44 dialysis units from three renal programs with several secondary objectives related to patient experience and outcomes.

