## Methods

### Study design

To date, the effect of PROMs on patient outcomes were generally assessed in conventional parallel-group RCTs of individuals. Few convincingly demonstrated benefits to patient-important outcomes, which might be in part due to contamination effects and small sample sizes [47]. This study uses a cluster RCT design, with clustering occurring at the level of individual hemodialysis units, to reduce potential contamination between the study groups (Fig. 1). EMPATHY is an open-label RCT, since blinding is not feasible [48]. Consequently, research staff, clinicians, and all patients are aware of group allocation. Dialysis units, stratified by three regions (Northern Alberta, Southern Alberta, and Ontario), were randomly allocated using random number sequences with all units from a region randomized on the same day. Dialysis units were allocated in a 1:1:1:1 ratio into four groups:
Group 1: Patients complete ESAS-r: Renal or IPOS-RenalGroup 2: Patients complete EQ-5D-5LGroup 3: Patients complete both ESAS-r: Renal or IPOS-Renal and EQ-5D-5LGroup 4: Usual care (i.e. the control group). To assess study outcomes, patients complete the PROMs at baseline, 6 and 12 months, but these data are not reported back to clinicians or patients.

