### Quantitative trial data analysis

The primary analysis will assess change in the overall CAT score, between study groups from baseline to 12 months using a linear mixed effects model, with the mean CAT for the dialysis unit at baseline as a fixed effect covariate, and dialysis unit (cluster) as a random intercept. Ideally, analysis should use individual patients’ baseline CAT and follow-up CAT rather than the unit mean baseline CAT to compute change over time. However, due to concerns by the regional renal programs to maintain anonymity of experience data as well as the natural drop-in and drop-out of patients in the dialysis units due to patient deaths and initiation of new patients onto dialysis, individual CAT surveys were made completely anonymous. As such, our primary analytic plan will be based on changes in mean CAT score at the unit level, from baseline to 12 months. The primary analysis will be based on all of the PROMs intervention groups combined compared to the control (no PROMs intervention) group as fixed effects. Any units that drop-out after randomization but prior to initial data collection will be excluded. We will employ last observation carried forward methods to impute missing data where appropriate. As one of our secondary objectives, assessing differences between specific and generic PROMs, we will compare the individual interventions groups (i.e., ESAS-r: Renal /IPOS alone, EQ-5D-5D alone, or the combination) to the control group.

As part of our secondary analyses, we will also compare the proportion of patients reporting symptoms/problems on the ESAS-r: Renal or IPOS-Renal and EQ-5D-5L and the management of such symptoms/problems. Through clinical records, we will link PROMs scores with the use of specific symptomatic treatments as per the treatment aids. We will obtain medication lists, allied health referrals, and chart notes to capture how symptoms are being treated. Because the PROMs data will be collected as part of the clinical record, and linked with individual patient-level data, we will be able to analyze these data using logistic mixed-effects regression models adjusting for individual patient-level covariates. Each renal program (i.e., AKC-N, AKC-S and ORN) will be analyzed separately then we will use meta-analyses to analyze the data from each renal program.

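### The stated 80% power for an effect size of 0.23 has no stated scale and does not follow from its inputs for the pooled primary contrast; the gap is modest in CAT points and large in SD units

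*Protocol article*

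**What the plan says.** Under Sample size and power, the article explains that the size was set by which units were eligible, and that no target sample size was calculated. It still gives a power statement. The inputs are "From 44 dialysis units, we will be utilizing data from approximately 3000 patients" and "Based on an estimated intraclass correlation of 0.1 and a standard deviation for the CAT (primary outcome measure) of 0.74", and the result is "this will provide 80% power to detect an effect size of 0.23 with a two-tailed test" at α = 0.05. The text goes on to call this effect small and to express confidence in the design nonetheless.

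Two other sections fix the comparison to which the figure should apply. Study design: "Dialysis units were allocated in a 1:1:1:1 ratio into four groups". Quantitative trial data analysis: "The primary analysis will be based on all of the PROMs intervention groups combined compared to the control". The latter section also puts the unit's mean baseline CAT in the model as a fixed-effect covariate.

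**The concern.** The power statement leaves out three things needed to check or use it: the scale of 0.23, the contrast and split of units behind it, and whether any gain from baseline adjustment is included. Pooling three of four equal groups gives a 3:1 split of units, which is less efficient than an even split. With an ICC of 0.1 and about 68 patients per unit, precision depends almost wholly on the number of units. A figure worked out without regard to the 3:1 split would therefore be too favourable.

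This is the article's only statement of how sensitive the primary comparison is. A reader of the results would use it to judge which differences the trial could have missed. On one reading of 0.23 the true power is somewhat below 80%; on the other it is about even odds.

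**Working it through.** **Inputs.** From Sample size and power: 44 units, N ≈ 3000, ICC ρ = 0.1, SD = 0.74, two-sided α = 0.05, 80% power. From Study design and Quantitative trial data analysis: k₁ = 33 and k₀ = 11 units, inferred from 1:1:1:1 allocation and the pooled contrast. Equal unit sizes and no covariate gain are assumed, since the power statement lists neither unequal sizes nor a baseline correlation.

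**Clustering.** m = 3000/44 = 68.18 patients per unit. Design effect = 1 + 67.18 × 0.1 = 7.72. Effective N = 3000/7.72 ≈ 389.

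**Standard error.** SE = SD × √[(ρ + (1 − ρ)/m)(1/k₁ + 1/k₀)] = 0.74 × √[(0.1 + 0.9/68.18)(1/33 + 1/11)] = 0.74 × √(0.1132 × 0.1212) = 0.74 × 0.1171 = 0.0867 points.

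**Attempt to reproduce 0.23.** Detectable difference (normal) = 2.8016 × 0.0867 = 0.243 points = 0.328 SD. With t on 42 df it is 0.249 points = 0.336 SD. Neither is 0.23.

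**Power for 0.23 at 33 v 11.**
- In points: 0.23/0.0867 = 2.653, and Φ(2.653 − 1.960) = 75.6% (t: 73.6%).
- In SD units: 0.23 × 0.74 = 0.1702 points, 0.1702/0.0867 = 1.963, and Φ(0.003) = 50.1% (t: 48.4%).

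**Other splits.** If groups are balanced within the strata of 17, 12 and 15 units, the control group could hold 10 to 12 units. The last two rows are not the primary contrast and are shown only as attempts to reproduce the figure.

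| Units | Detectable, points (normal) | Power for 0.23 points (normal / t) | Power for 0.23 SD (normal / t) |
|---|---|---|---|
| 33 v 11 | 0.243 | 75.6% / 73.6% | 50.1% / 48.4% |
| 32 v 12 | 0.236 | 77.9% / 76.0% | 52.4% / 50.5% |
| 34 v 10 | 0.251 | 72.8% / 70.9% | 47.6% / 45.9% |
| 22 v 22 | 0.210 | 86.5% / 84.9% | 62.1% / 60.1% |
| 11 v 11 | 0.297 | 58.2% / 54.1% | 36.1% / 33.3% |

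No row gives 80% on either scale.

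**Limit with more patients.** As m grows without bound, SE tends to √(0.1 × 0.1212) = 0.1101 SD. Power for 0.23 SD is then capped at 55.1% (t: 53.2%), and the smallest effect detectable at 80% power is 2.8016 × 0.1101 = 0.308 SD.

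**Baseline adjustment.** If unit means at baseline and follow-up correlate at r, the variance is multiplied by about 1 − r². Reaching 80% needs:
- 0.23 points: 1 − r² = (0.23/0.2428)² = 0.897, so r ≈ 0.32. With t, (0.23/0.2486)² = 0.856, so r ≈ 0.38.
- 0.23 SD: 1 − r² = 0.491, so r ≈ 0.71.

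**Rounding of the ICC.** At ρ = 0.09, 33 v 11 (normal): 2.8016 × 0.74 × √[(0.09 + 0.91/68.18) × 0.1212] = 0.232 points. At ρ = 0.11 the same formula gives 0.253. To reach 80% for 0.23 SD, ρ would have to be about 0.042.

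**The case against.** The best defence is that 0.23 is in CAT points. A standardised effect needs no SD, yet the text supplies one. Calling the effect small does not decide the matter, because 0.23/0.74 = 0.31 SD can also be called small. On that reading the shortfall is 0.013 points (0.019 with t), and the inputs are coarse: an estimated ICC printed to one decimal, an approximate patient count, and a split that is itself inferred. An ICC of 0.09 would give 0.232. The planned baseline covariate could also recover 0.23 points at a modest correlation. Finally, the figure set no design parameter.

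Most of this stands, and it limits the point. It does not make the figure right. Rounding can go either way, no baseline correlation is stated, and the printed inputs still give 74 to 76% for the nominal split. Nor does rounding rescue the SD reading, which would need an ICC of about 0.042.

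A reader might infer that 0.23 is beyond the trial's reach however many patients it includes. The document does not support that as a general statement. It holds only if 0.23 is in SD units and no credit is taken for the planned covariate; a unit-level correlation of about 0.71 would reach it. A reader might also want to count incomplete survey response, unequal unit sizes and the missing power for single-group comparisons. The article gives no figures for the first two, and all three are details that a condensed article may leave to the full protocol or analysis plan. They are not part of this point.

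**Conclusion.** The power statement is incomplete, and on its stated inputs it is wrong for the primary contrast. At 33 v 11 units without covariate gain, 80% power corresponds to about 0.24 to 0.25 CAT points (0.33 to 0.34 SD), not 0.23 on either scale. On the likelier reading, in points, the error is modest and close to the rounding of the ICC. On the SD reading it is large, and more patients per unit would not repair it without baseline adjustment.

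This rests on the nominal 33 v 11 split, equal unit sizes, an ICC of exactly 0.1 and data from about 3000 patients. The calculation method is cited to a source that is not at hand, so how 0.23 arose cannot be determined. Severity is moderate: the published sensitivity figure needs correcting, but the number of units and patients was fixed by availability and is unaffected.

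**What to change.** State whether 0.23 is in CAT points or SD units, and say that the figure refers to the pooled intervention groups against control, nominally 33 v 11 units. Then do one of two things:

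- Restate the result: with an ICC of 0.1 and an SD of 0.74, the trial has 80% power for about 0.25 CAT points (0.34 SD) before baseline adjustment.
- If 0.23 takes credit for adjusting for unit mean baseline CAT, keep it and state the assumed unit-level correlation and its source.

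If the ICC was carried at more decimals than printed, give the value used. The cost is a sentence or two. Under the first option the stated figure becomes slightly less favourable. Enrolment, conduct and the analysis model do not change.

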### Quantitative trial data analysis

The primary analysis will assess change in the overall CAT score, between study groups from baseline to 12 months using a linear mixed effects model, with the mean CAT for the dialysis unit at baseline as a fixed effect covariate, and dialysis unit (cluster) as a random intercept. Ideally, analysis should use individual patients’ baseline CAT and follow-up CAT rather than the unit mean baseline CAT to compute change over time. However, due to concerns by the regional renal programs to maintain anonymity of experience data as well as the natural drop-in and drop-out of patients in the dialysis units due to patient deaths and initiation of new patients onto dialysis, individual CAT surveys were made completely anonymous. As such, our primary analytic plan will be based on changes in mean CAT score at the unit level, from baseline to 12 months. The primary analysis will be based on all of the PROMs intervention groups combined compared to the control (no PROMs intervention) group as fixed effects. Any units that drop-out after randomization but prior to initial data collection will be excluded. We will employ last observation carried forward methods to impute missing data where appropriate. As one of our secondary objectives, assessing differences between specific and generic PROMs, we will compare the individual interventions groups (i.e., ESAS-r: Renal /IPOS alone, EQ-5D-5D alone, or the combination) to the control group.

As part of our secondary analyses, we will also compare the proportion of patients reporting symptoms/problems on the ESAS-r: Renal or IPOS-Renal and EQ-5D-5L and the management of such symptoms/problems. Through clinical records, we will link PROMs scores with the use of specific symptomatic treatments as per the treatment aids. We will obtain medication lists, allied health referrals, and chart notes to capture how symptoms are being treated. Because the PROMs data will be collected as part of the clinical record, and linked with individual patient-level data, we will be able to analyze these data using logistic mixed-effects regression models adjusting for individual patient-level covariates. Each renal program (i.e., AKC-N, AKC-S and ORN) will be analyzed separately then we will use meta-analyses to analyze the data from each renal program.

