### Setting and population

Dialysis programs frequently provide administrative functions for separate hemodialysis units; however, the unit of randomization is the dialysis unit, not dialysis programs or individual patients. In total, 44 units from three renal programs were randomly allocated to one of the four study groups. We enrolled all eligible hemodialysis units in Alberta, including 17 hemodialysis units from the Alberta Kidney Care - North (AKC-N) program and 12 units from the Alberta Kidney Care - South (AKC-S) program. Of Ontario’s 92 hemodialysis units, 15 enrolled in the study, based on voluntary acceptance of invitation to participate.

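### The stated primary CAT model omits region, the factor the units were randomised within, so the test may be conservative and less precise than the design allows

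*Protocol article*

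**What the plan says.** The Study design section of the protocol article states: "Dialysis units, stratified by three regions (Northern Alberta, Southern Alberta, and Ontario), were randomly allocated using random number sequences". It adds that "Dialysis units were allocated in a 1:1:1:1 ratio into four groups". Setting and population reports that "44 units from three renal programs were randomly allocated to one of the four study groups", made up of "17 hemodialysis units from the Alberta Kidney Care - North (AKC-N) program and 12 units from the Alberta Kidney Care - South (AKC-S) program", with the other 15 in Ontario.

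The section on quantitative trial data analysis describes the primary analysis as a linear mixed effects model of the overall CAT score from baseline to 12 months. It compares the three PROM groups combined with control, "with the mean CAT for the dialysis unit at baseline as a fixed effect covariate, and dialysis unit (cluster) as a random intercept". No region or program term is listed.

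The next paragraph covers the secondary analyses of symptoms and their management by logistic mixed models. It ends: "Each renal program (i.e., AKC-N, AKC-S and ORN) will be analyzed separately then we will use meta-analyses". The article does not say whether that sentence also governs the primary analysis.

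**The concern.** When units are allocated within strata, differences between strata are largely balanced across arms and contribute little to the sampling error of the treatment contrast. A model without the stratum still counts those differences as unexplained between-unit variation. Its standard error then exceeds the true one, the test rejects less often than its nominal level, and precision that the stratification provided is lost.

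Region is plausibly related to the outcome here. Table 1 shows that the programs differ in disease-specific PROM, report cards, treatment aids and survey mode. Alberta enrolled all its eligible units, while Ontario enrolled 15 volunteers out of 92. Under Study timelines, the programs start at different dates. Some of this, such as the start date, could affect change from baseline as well as baseline level.

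The two paragraphs of the analysis section also treat region differently without explanation: the primary model does not mention it, and the secondary analyses are split by it. The split leaves few units per arm within each program.

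**Working it through.** **Inputs.** From Sample size and power: ICC 0.1, SD 0.74, about 3000 patients, 44 units, 80% power for an effect of 0.23, two-sided alpha 0.05. From Setting and population: 17, 12 and 15 units. The primary contrast is nominally 33 v 11 units (44 x 3/4 and 44 x 1/4).

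**The plan's own figure.** Patients per unit m = 3000/44 = 68.18. Design effect = 1 + 67.18 x 0.1 = 7.718. With 2250 v 750 patients, SE = 0.74 x sqrt(7.718 x (1/2250 + 1/750)) = 0.0867. Taking 0.23 as raw CAT points, power = Phi(0.23/0.0867 - 1.96) = 75.6%, and the detectable difference is (1.96 + 0.84) x 0.0867 = 0.243. An even 22 v 22 split has SE 0.0751 and power 86.5%. Neither gives 80%. That is a separate matter, but it shows that the primary contrast has no precision to spare.

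**Cost of omitting region when baseline does not capture it.** Let q be the share of between-unit variance that lies between regions (assumed). In units of SD squared, the variance of a unit mean is 0.1 + 0.9/68.18 = 0.1132. With balance across regions, the part that affects the contrast is 0.1(1 - q) + 0.0132. The ratio of true to estimated SE is r = sqrt of the second over the first, and type I error is 2(1 - Phi(1.96/r)).

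| q | r | SE too large by (1/r - 1) | Type I error | Detectable difference with region (0.243 x r) |
|---|---|---|---|---|
| 0.1 | 0.955 | 5% | 0.040 | 0.232 |
| 0.2 | 0.907 | 10% | 0.031 | 0.220 |
| 0.3 | 0.857 | 17% | 0.022 | 0.208 |

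**Simulation check.** The formula ignores the baseline covariate and assumes exact balance, which 17 and 15 units over four arms cannot give. Unit-level analyses of covariance were therefore simulated with 17/12/15 units allocated within region, 33 v 11, baseline unit mean included and a t reference.

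- *Region has no effect:* type I error 5.4% without and 5.3% with region; mean SE 0.069 in both. No loss.
- *Baseline mean carries the regional difference (share 10, 25, 50%):* mean SE without v with region is 0.0668 v 0.0662, 0.0635 v 0.0620 and 0.0574 v 0.0543, that is 1%, 2% and 6% larger. Type I error without region is 4.0-4.8%.
- *12-month regional differences unrelated to baseline (share 10-50%):* type I error is 1.8-4.3% without region and 4.8-5.4% with it. Power at 0.23 is 74-83% without and 77-96% with region. At a 25% share the formula gives r = 0.883 and type I error 0.026; the simulations gave 0.031 and 0.026 (unit-level baseline correlation 0 and 0.5).

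**Units behind the program-level fits.** At 1:1:1:1 the nominal counts per arm are 17/4 = 4.25, 12/4 = 3 and 15/4 = 3.75. In AKC-S, combined arms v control leaves 12 - 2 = 10 unit-level degrees of freedom, with a t critical value 1.137 times 1.96. With all four arms in the model, 12 - 4 = 8 remain. The reference distribution therefore matters, but the article does not name one.

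**The case against.** Three points on the other side carry weight.

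- **The baseline mean may do the work.** It is in the model and may absorb most of the regional difference. The 5-17% figure ignores it and rests on a regional variance that the article does not give. This stands: the figure is conditional, and the loss may be 1-6% or nothing.
- **Region may already be handled.** The sentence on separate analysis by program closes the whole analysis section. If it was meant to cover the primary analysis, region is dealt with there. By position it belongs to the secondary paragraph, so the scope needs stating. An analysis plan not shown might also include region, but the article does list the primary model's terms, and region is not one of them.
- **The secondary analyses are not shown to be faulty.** A reader might infer that their tests reject too often. Type I error of roughly 9-22% can be produced by assuming Wald z inference and fixed-effect pooling. The article specifies neither, and these choices commonly sit in an analysis plan. The upper part of that range also requires discarding two of the four arms. With all four arms kept, a simulation on unit means gave 9.7% under fixed-effect and 6.1% under random-effects pooling, still with z inference. Fitting by program and then pooling respects the stratified allocation and has a reason: AKC-S uses a different disease-specific instrument. One-stage or two-stage analysis is largely a matter of preference.

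**Conclusion.** The point holds for the primary model and is one of precision, not validity. Region was used to randomise and is missing from the listed terms. Under an assumed 10-30% regional share of between-unit variance beyond baseline, the SE is about 5-17% too large and type I error is 0.040-0.022. The loss is about 1-6% if baseline carries the regional difference (shares up to 50%) and nil if region does not matter. The documents do not show which case applies.

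A reader might conclude that the error bars are wrong in both the primary and the secondary analyses. The documents do not support that. In the primary analysis the omission is at worst conservative and adds no false-positive risk. In the secondary analyses the method is not specified far enough to call the intervals too narrow. What remains there is a caution: with nominally three units per arm in AKC-S and about four in each of the other two programs, small-sample inference is needed. Actual counts by region and arm are not given.

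**What to change.** - Add region (Northern Alberta, Southern Alberta, Ontario) as a fixed effect in the primary CAT model, beside study group, unit baseline mean and the unit random intercept. The cost is two degrees of freedom from 44 units and one line of text.
- State whether the sentence on separate analysis of each renal program applies to the primary analysis or only to the secondary ones.
- For the secondary program-level fits, state small-sample degrees of freedom and the pooling method. The two-stage approach can stay, and program-specific estimates remain available. This costs only wording, or a cross-reference if the analysis plan already covers it.
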